### Maintenance

To evaluate the final construct in the RE-AIM framework, the following methods will be completed: determine percent of community coalitions indicating that EPICS will become standard practice; measure program feasibility, including cost, time, and human resources for program implementation; determine if EPICS facilitator training and curriculum is offered to additional settings; investigate the extent to which EPICS is integrated into community coalition planned activities; measure enablers and barriers to continued EPICS implementation and plans to continue or ‘intent’ to offer; determine number of clusters and settings who had once offered EPICS but stopped; and determine the extent to which churches, clinical providers and community sites continue EPICS sessions post-implementation. Logistic regression analysis will evaluate variations in the effects of implementation barriers among community coalitions and settings. Descriptive statistics will determine setting by type and number completing facilitator training.

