### Community coalitions

The community coalitions that will serve as clusters in the EPICS cRCT are part of the National Black Leadership Initiative on Cancer (NBLIC), a network that was founded in 1987 and have primarily engaged in community education efforts; this history has been described elsewhere [11]. The coalitions include individuals from academia, business, health care, non-profit organizations, and other community stakeholders. Twenty of the 33 NBLIC community coalitions will be randomized as clusters in the EPICS cRCT. In developing this project, we executed Memoranda of Understanding (MOU) between the coalitions and Morehouse School of Medicine; recruited research sites and surveyed the community coalitions’ organizational characteristics.

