### Sample size calculation

We intend to enroll 7,200 individuals in this study, with 1,800 enrolled in each study arm. This sample size is based on 20 NBLIC community coalitions randomized to four study arms (WA, WA + TA, IP, IP + TA). There will also be three settings (church, clinic, and community site) per coalition. Each community coalition will have 30 groups of individuals completing three consecutive EPICS sessions, recruiting 15 individuals per setting with an expected 25% dropout rate; thus, we anticipate that 12 of these individuals will complete all three sessions. For the EPICS cRCT, there will be (30 groups of three sessions) × (12 individuals completing all three sessions) × (20 NBLIC community coalitions) = 7,200 individuals. Based on data from a previously published study, we calculated intracluster correlation coefficient (ICC) to equal 0.0911 (9.1%) [6]. The effective sample size (ESS) was 5,645, which still has high power (>99%) with design effect of 1.2754.

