### Power analysis

Power calculations were performed to further justify our proposed sample size. All of these assume a sample size of 1,800 per study arm, a significance level of 5% (*i.e.* alpha = 0.05), and a two-sided two-group chi-square test of proportions. Calculations were performed using nQuery Advisor, version 7. These are performed for hypothesis one (H1) and hypothesis three (H3); hypothesis two (H2) is qualitative, so power calculations do not apply. For H1, we anticipate that there will be 25%, 33%, and 50% greater participant enrollment with the Web + TA arm, IP arm, and IP + TA arm, respectively, when compared to the passive web-based-only arm (based on our prior experience with community coalition based studies). Comparisons of any of these proportions to any proportion that is obtained for the passive web-based arm (for example, 5%, 10%, or 20%) will result in greater than 99% power to detect differences in the proportions as being statistically significant. For H3, we can obtain estimates of cancer knowledge change over time (pre-intervention to post-intervention percentages with the correct response) for a small group education cohort and a control cohort from Blumenthal, Smith *et al.*[6]. These estimates include changes of 34.8 (71-36) and 15.5 (55.2-39) for a CRC perceived risk question, and 22.9 (92.9–70) and 13.1 (88.5–75.for a CRC screening question. Assuming that we observe similar changes in our study participants for active and passive arms, we will have greater than 99% power to detect differences in the proportions as being statistically significant.

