### Adoption

In evaluating adoption, methods include: determining EPICS fit, cost, level of resources and expertise and similarity to current programs; estimating adoption rate (proportion of community coalitions trained that implement EPICS); and documenting reasons for not adopting EPICS (time, total membership or infrastructure, partnerships, program priorities). Descriptive statistics will be used to provide insight into organizational and individual reasons for (not) adopting EPICS. Differences between community coalitions adopting and not adopting EPICS and differences between facilitator characteristics will be analyzed using independent sample *t* tests and chi-square tests.

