### Implementation

To evaluate EPICS implementation, the following methods will be employed: train and certify facilitators to deliver educational sessions; implement marketing strategies to enhance visibility; provide on-going technical assistance (TA) to organizations and settings; determine adherence to implementation protocol by passive and active dissemination sites; estimate total number of completers; conduct one-and-one-half day training guided by three modules: principles, procedural and practical knowledge; distribute a monthly newsletter, provide promotional flyers and posters to community coalitions and settings; conduct one-hour monthly teleconferences; assess the nature and quality of TA; measure level of fidelity to delivering sessions as developed; and determine total number of individuals completing the three educational intervention sessions. Descriptive statistics will determine differences in facilitator characteristics, knowledge, attitudes, and beliefs and level of satisfaction with training, the most effective marketing strategies, reasons for not implementing components, duration, and investment and differences facilitator demographic characteristics: education, gender, profession, insurance status, etc. Logistic regression analysis will evaluate variations in the effects of implementation barriers among community coalitions, settings and individual participants.

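### Coalition-level logistic regression on at most 20 records will often have no finite estimate, and chi-square tests of adopting versus non-adopting coalitions are unreliable at that size

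*Protocol article*

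**What the plan says.** All references are to the protocol article.

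- **Number of coalitions.** Community coalitions: "Twenty of the 33 NBLIC community coalitions will be randomized as clusters in the EPICS cRCT".
- **Maintenance.** "Logistic regression analysis will evaluate variations in the effects of implementation barriers among community coalitions and settings". One outcome listed there is the percentage of coalitions that say EPICS will become standard practice, which is a yes/no result per coalition. Secondary outcome measures places maintenance at the level of the change agent or cluster and rules out measuring it in individuals.
- **Implementation.** "Logistic regression analysis will evaluate variations in the effects of implementation barriers among community coalitions, settings and individual participants".
- **Adoption.** "Differences between community coalitions adopting and not adopting EPICS and differences between facilitator characteristics will be analyzed using independent sample" t tests and chi-square tests. No regression is planned here. Reasons for not adopting are to be summarised descriptively.
- **Settings.** Sample size calculation: "There will also be three settings (church, clinic, and community site) per coalition".

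The article gives no number of barriers per model, no expected rate of adoption or continuation, no small-sample method and no chi-square variant. A two-sided 5% level is stated only for the power calculations of hypotheses one and three.

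**The concern.** For a yes/no outcome recorded once per coalition, the sample is the number of coalitions, not the 7,200 participants. Two named methods meet that small number.

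Logistic regression fitted by maximum likelihood has no finite solution when the barriers separate, fully or partly, the coalitions with the outcome from those without it. Software then prints very large odds ratios or fails to converge. With 20 records this is common.

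The chi-square test relies on an approximation that needs adequate expected counts. With 20 coalitions these are almost never reached.

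At stake is what the trial can say about which barriers go with coalitions delivering EPICS as planned and keeping it going. The Trial timeframe gives 18 months to assessing maintenance.

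**Working it through.** **Inputs from the article.** 20 coalitions and three setting types per coalition. The only stated figure that uses the number of coalitions reproduces: 30 × 12 × 20 = 7,200.

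**Assumptions, shown as ranges.** Outcome rate 50%, 70%, 80% or 90%. Barriers are yes/no, independent, present in half of coalitions, with no true effect. The number of barriers is one or four; four is the number of reasons named under Adoption and serves only as an illustration.

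**1. One barrier, n = 20.** There is no finite estimate when any cell of the 2×2 table is empty. Let q = 0.5 × (1 − outcome rate) be the probability of each of the two rarer cells. For rates of 70% and above, the probability that at least one of them is empty is 2(1 − q)^20 − (1 − 2q)^20, and the other two cells add almost nothing.

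- Rate 70%, q = 0.15: 2 × 0.0388 − 0.0008 = 7.7%
- Rate 80%, q = 0.10: 2 × 0.1216 − 0.0115 = 23.2%
- Rate 90%, q = 0.05: 2 × 0.3585 − 0.1216 = 59.5%
- Rate 50%, where all four cells have probability 0.25: about 4 × 0.75^20 = 4 × 0.0032 = 1.3%

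Simulation agrees within its error (1%, 8%, 20% and 61% at 50%, 70%, 80% and 90%).

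**2. Four barriers, n = 20.** Separation was checked by linear programming in simulated data sets.

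| Outcome rate | No finite estimate (range over runs) |
|---|---|
| 50% | 12-13% |
| 70% | 28-33% |
| 80% | 50-53% |
| 90% | 84-86% |

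With barriers present in 30% of coalitions the figures are 33%, 52%, 75% and 94%. With a true log odds ratio of −1 for each barrier (prevalence 50%) they are 35%, 44%, 63% and 85%.

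**3. Tests from the four-barrier model, n = 20.** At outcome rates of 50% and 80%, the nominal 5% likelihood-ratio test rejects a true null 10% and 13% of the time, and the Wald test 1.7% and 0.4%. The error rate therefore depends on which test the software reports.

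**4. Setting level.** 20 × 3 = 60 settings, taking one of each type per coalition. If they are treated as independent, four-barrier separation is at most 1.4% at rates of 50-70%, 1-9% at 80% and 23-46% at 90%. Settings are nested in coalitions, however. For a coalition-level barrier the design effect is 1 + (3 − 1) × ICC. Borrowing the article's ICC of 0.0911 gives 1.18; an assumed 0.3 gives 1.6. In simulation with a 70% outcome rate, an unadjusted two-sample test has size 7.2% and 12.4% respectively.

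**5. Chi-square, 20 coalitions.** The smallest expected count is a × b / 20, where a and b are the smaller margins, each at most 10. It reaches 5 only if a × b ≥ 100, that is a = b = 10.

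Size of the uncorrected Pearson test given the margins:

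- Margins 5 and 8: tables with 0, 4 or 5 in the joint cell are rejected (chi-square 4.44, 4.44 and 10). Probability (792 + 840 + 56)/15,504 = 10.9%.
- Margins 1 and 4: a joint cell of 1 gives chi-square 4.21, with probability 4/20 = 20%.
- Margins 1 and 5: the largest chi-square is 3.16, below 3.84, so the size is 0.

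Over all 361 margin pairs the size runs from 0 to 20% and exceeds 5% in 144. With the group split fixed and the outcome random, it is at most 4.2% for 10/10, 5.9% for 12/8 and 9.1% for 18/2. Averaged over random splits it is 2.3% to 5.1%. With the Yates correction it is at most 1.3%. Fisher's exact test stays between 0.03% and 3.2%.

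**The case against.** The strongest reply is that the article does not commit to a 20-record multivariable model. Its sentences cover settings, and under Implementation also participants; they list no regressors and do not say that barriers enter together. Secondary analyses in a condensed article may be specified elsewhere. This limits the point but does not remove it: coalitions are named as a level of analysis, maintenance is placed at cluster level, and a single barrier already separates often once the outcome is common.

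A reader might also infer more than the text supports:

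- **That adoption will be modelled by logistic regression on four barriers.** The Adoption section plans t tests, chi-square tests and description only.
- **That chi-square generally fails to hold 5%.** It does so at some margins. Averaged over outcomes it is mostly at or below 5-6%.
- **That most coalitions will continue because memoranda were signed.** The article gives no such rate.
- **That the effectiveness result depends on these models.** Screening adherence is analysed by GEE, and none of the three hypotheses or power claims uses the barrier regressions.
- **That adoption always means at most 20 coalitions.** Secondary outcome measures counts coalitions approached, so up to 33 could enter; the Adoption section counts coalitions trained. If all 33 were approached and 13 did not take part, expected counts of 5 would still require a smaller margin of at least 13 on the characteristic (13 × 12/33 = 4.7; 13 × 13/33 = 5.1).

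**Conclusion.** The point holds for coalition-level analyses. A logistic model of a yes/no implementation or maintenance outcome has at most 20 records. At outcome rates of 50-90% and barrier prevalence of 50%, it has no finite maximum-likelihood estimate in about 12-86% of data sets with four barriers and about 1-60% with one. The low end applies when the outcome splits evenly, the high end when nearly all coalitions share it. These figures rest on assumed rates, prevalence and number of barriers, and on reading unqualified logistic regression as maximum likelihood.

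The chi-square comparison of adopters with non-adopters is a separate and milder matter. Its p-values are unreliable in either direction because expected counts fall below 5, but a general excess of false positives is not shown. Setting-level models separate much less often; their weakness is that no allowance for coalition clustering is stated. All of this concerns secondary, explanatory analyses.

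**What to change.** State in the Adoption, Implementation and Maintenance analyses that:

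1. Coalition-level comparisons of yes/no outcomes use Fisher's exact or permutation tests.
2. Coalition-level regressions use Firth-penalised logistic models with one barrier at a time, labelled exploratory. No multivariable model is fitted to 20 coalition records.
3. Where barriers or outcomes vary by setting or participant, the logistic model includes a coalition random effect or an equivalent cluster adjustment, so that records are not treated as independent.

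The cost is wording only, since the data are already to be collected. The drawbacks are that exact tests are conservative (Fisher's size was at most 3.2% in the cases examined) and that the factor analyses are reported as exploratory. The Firth method gives finite estimates under separation; its error rate at n = 20 was not calculated here.

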### Trial timeframe

The EPICS cRCT is planned from May 2012 until March 2017. In months one to three, the EPICS Coordinating Center will be established and monthly teleconferences, between the MSM research team and NBLIC community coalitions, will take place. Community coalitions will be randomized into four study arms. Recruitment of community settings (*e.g.*, churches, clinics, and community sites) and potential facilitators by community coalitions and baseline CRC screening rates for each targeted community will also be completed during this time. From months four to seven, facilitator training/certification will be completed, followed by a four-month pilot period (months eight to twelve). The implementation phase, months 13 to 36, includes delivery of three educational sessions and follow-up to determine CRC screening status of 7,200 African Americans in 13 US states to evaluate EPICS adoption and effectiveness. The final 18 months of the active study (months 37–54) will be dedicated to assessing EPICS maintenance. The final six months (54–60) will be reserved for data analysis, publications, and reporting.

### Trial status

The EPICS cRCT completed its pilot phase February 28, 2013. The Implementation Phase will begin May 1, 2013.

## Discussion

Implementing EPICS in partnership with community coalitions, we hypothesized, will result in more rapid adoption than traditional top-down approaches, and that changes in community CRC screening practices are more likely to be sustainable over time. With its national reach, this study has the potential to enhance our understanding of barriers and enablers to the uptake of educational programs aimed at eliminating cancer health disparities.

Glasgow *et al.* at the National Institutes of Health (NIH) have stated: ‘there is a need for research testing approaches to scaling up and sustaining effective interventions’ [25]. This project will help address that need and will focus on the five core values cited by Glasgow *et al.*: rigor and relevance, efficiency, collaboration, improved capacity, and cumulative knowledge. Regarding the first, the project will utilize the rigorous research methods required of NIH-funded studies; but of equal importance, it will test dissemination in settings that are similar to those in communities across the country, where they often serve African Americans. The project is efficient in that it tests several settings simultaneously. It involves widespread collaboration through its reliance on community coalitions that are comprised of healthcare professionals, business people, lay advocates, cancer survivors, and others. The project is building improved capacity in these coalitions; as a consequence, they will be prepared to participate in other cancer prevention studies in the future. The project is the product of cumulative knowledge developed through the original community intervention trial, the local practice demonstration, and the statewide initiative. These multiple iterations made possible the current study. The current study should be the last iteration; at its conclusion, EPICS will be positioned to become a part of standard health promotion practice.

## Abbreviations

ACS: American Cancer Society; BRFSS: Behavioral Risk Factor Surveillance System; CCSIT: Colorectal Cancer Screening Trial; CDC: Centers for Disease Control and Prevention; CRC: Colorectal cancer; cRCT: Cluster randomized controlled trial; EPICS: Educational Program to Increase Colorectal Cancer Screening; DNA: Deoxyribonucleic acid; FOBT: Fecal occult blood test; GCC: Georgia Cancer Coalition; GEE: Generalized Estimating Equation; H1: Hypothesis one; H2: Hypothesis two; H3: Hypothesis three; ICER: Incremental Cost Effectiveness Ratios; IP: In-person; IRB: Institutional Review Board; MOU: Memorandum of Understanding; MSM: Morehouse School of Medicine; NBLIC: National Black Leadership Initiative on Cancer; NCI: National Cancer Institute; RCCG: Regional Cancer Coalitions of Georgia; RE-AIM: Reach, Effectiveness, Adoption, Implementation, Maintenance; RTIPs: Research Tested Intervention Programs; TA: Technical assistance; WA: Web-access.
